### Outcomes 

The primary endpoint will be either death or liver decompensation (composite endpoint). Liver decompensation will be detected clinically (ascites, jaundice, encephalopathy, upper gastrointestinal bleeding). Deaths will be verified by health extension workers, who will trace/identify patients WHO miss appointments for more than 3 months. Health extension workers are individuals with a minimum of 10^th^ grade schooling who are part of the Ethiopian public health extension program. Each village has two health extension workers whose main responsibility is to deliver preventative and promotive health services at community level.

Secondary endpoints include programmatic outcomes (linkage to care, retention in care) and laboratory outcomes (viral suppression *viz*HBV DNA ≤10 IU/ml; new HIV infection). HBV DNA is not part of routine care at these sites but will be collected using dried blood spots (DBS) during the study period and measured after completion of the observation period (three years) for those who have received treatment, using the Xpert HBV viral load kit (Cepheid, CA, USA). 

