## Background

Although the number of people newly infected by chronic hepatitis B (CHB) has declined in recent years, the estimated number of deaths due to CHB is increasing [1]. Over 60% of new hepatitis B infections occur in the World Health Organization (WHO) African region, but only 4% of people living with CHB have been tested in the same region [1]. Furthermore, treatment with Tenofovir disoproxil fumarate (TDF) or other nucleos(t)ide analogues (NA) can effectively prevent liver fibrosis and liver disease [2, 3], but only 0.2% of the estimated population with CHB in the WHO African Region are reached with treatment [1].

As identified by the WHO, a key challenge for LMICs to improve testing and treatment, is decentralization of care [1]. In Ethiopia, hepatitis B treatment and care is only available in larger cities [4, 5], while the majority of the population are living in rural areas [6]. With a population exceeding 100 million, and a hepatitis B prevalence at 6.0% [7], decentralized models of care are needed to reduce liver-related mortality. However, international CHB guidelines may not apply in this setting since modern tools such as hepatitis B virus (HBV) deoxyribonucleic acid (DNA) testing, liver stiffness measurements (LSM) or liver biopsy [8, 9] are unavailable in rural areas of Ethiopia. Previous studies have demonstrated how the lack of these tools can act as barriers to care [10]. Although the WHO has published an updated guideline with a simplified treatment algorithm [11], models of care suited to rural populations in LMICs with limited laboratory services and lack of specialized healthcare personnel are yet to be assessed. If the WHO elimination goals for viral hepatitis are to be reached [12], new models of CHB care tailored to these populations are needed.

In this study, we aim to test and compare three models of care at the primary care level in rural Ethiopia, and to explore and identify the best ways to implement CHB care and treatment in this setting. By testing three different models of care, and assesing both clinical and programmatic outcomes, we aim to identify the model of care best suited to rural poulations in LMICs. Furthermore, we plan to evaluate the implementation process, to identify barriers and facilitators, and to understand how to best implement a complex intervention in a resource-limited setting [13–16].

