## Methods

### Study design

This will be prospective cohort study comparing three models of decentralized care for the management of CHB in Ethiopia. The overreaching research question is “What is the best model of care for testing, treatment, and follow-up in a primary hospital/health center in rural Ethiopia”. The three models of care will be assessed both from a clinical, programmatic and implementation perspective.

Testing, screening and linkage to care is common for the three model, but the treatment protocol differs. The standard model utilizes the WHO 2024 treatment guideline for hepatitis B to identify individuals at *high risk* of disease progression («*treat only if.*.») [11]. As most primary hospitals in Ethiopia lack assess to HBV DNA testing, we will use the WHO treatment eligibility criteria for settings without an HBV DNA analysis option (Table 1). The simplified model will utilize clinical and laboratory criteria to identify patients at *low risk* of liver injury, who will be exempted from treatment («*treat all except …*»). Finally, the test-and-treat model will offer treatment to all individuals with CHB (“*treat all*”), mimicking the models of care that have been successfully assessed and implemented for HIV and hepatitis C [17]. This latter model avoids the complicated patient assessment and the demand for expensive laboratory tests.

**Table 1 Tab1:** The three models of care to be assessed in the study: treatment criteria, laboratory analyses required, and scheduled follow-up

	Standard model “treat only if…”	Simplified model “treat all except…”	Test and treat model “treat all”
Treatment criteria	Treat *only* if:	Treat all, *except* if:	Treat all
	-Clinically diagnosed cirrhosis	-There are no signs, symptoms or risk factors for liver disease, *AND*	
	-APRI above 0.5	-APRI is 0.3 or below	
	-Persistently elevated ALT		
	-Co-infections and co-morbidity		
	Pregnant women: treat to prevent mother-to-child transmission		
Laboratory analysis required at inclusion	AST, ALT, platelets, (Creatinine^1^)	AST, platelets (Creatinine^1^)	(Creatinine^1^)
	HIV, HCV, HBsAg RDTs	HIV, HCV, HBsAg RDTs	HIV, HCV, HBsAg RDTs
Follow-up:on treatment	Physical examination, HIV, and pharmacy refill at 3 months, then every 6 months	Physical examination, HIV, and pharmacy refill at 3 months, then every 6 months	Physical examination, HIV and pharmacy refill at 3 months, then every 6 months

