	AST, ALT, platelets, (creatinine^1^), HBsAg, DBS every 12 months	AST, platelets, (creatinine^1^), HBsAg, DBS every 12 months	(Creatinine^1^), HBsAg, DBS every 12 months
Follow-up:*not* on treatment	Physical examinationAST, ALT, plateletsHBsAg,DBSevery 6 months	Physical examinationAST, plateletsHBsAg,DBSevery 6 months	N/A

*Abbreviations**: ALT* alanine aminotransferase, *APRI* aspartate aminotransferase to platelets ration, *AST* aspartate aminotransferase, *HCV* hepatitis C virus, *HbsAg* hepatitis B surface antigen, *HIV* human immunodeficiency virus, *DBS* dried blood spot testing, *N/A* Not applicable, *RDT* rapid diagnostic test

^1^ Only required in patients at risk of renal disease, i.e. individuals with hypertension, diabetes, use of nephrotoxic drugs, or age above 60 years

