### Objectives

*Study clinical efficacy (death*,* liver decompensation) of different models of decentralized CHB care*.*Study programmatic success indicators (linkage to care*,* loss to follow-up) with different models of decentralized CHB care*.*Evaluate the implementation of CHB care (Context*,* process*,* and outcomes) of different models*.*Study laboratory success indicators (suppression of viral load*,* human immunodeficiency virus (HIV) incidence) in different models of decentralized CHB care*.*Compare all outcome indicators (points 1–3 above) of decentralized care with the results of hospital-based care from similar settings*.*Study the effect of community screening for hepatitis B*.

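### HBV DNA is assayed only in treated patients, whom each model selects by its own rule, so treated-only suppression cannot be read as a comparison of the models

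*Protocol article*

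**What the plan says.** The Outcomes section gives the laboratory secondary endpoints as viral suppression and incident HIV ("HBV DNA ≤10 IU/ml; new HIV infection"). HBV DNA comes from dried blood spots (DBS) and is to be "measured after completion of the observation period (three years) for those who have received treatment".

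The fourth item under Objectives begins "Study laboratory success indicators (suppression of viral load" and refers to the different models of decentralized care. The Background states the general purpose: "we aim to test and compare three models of care at the primary care level in rural Ethiopia".

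Study design explains what separates the models: "Testing, screening and linkage to care is common for the three model, but the treatment protocol differs". Table 1 gives the rules:

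- Standard: meant to "identify individuals at *high risk* of disease progression". Treatment requires clinical cirrhosis, "APRI above 0.5", persistently raised ALT, or co-infection or co-morbidity.
- Simplified: all are treated unless they have no signs, symptoms or risk factors and their APRI is at most 0.3.
- Test-and-treat: all are treated.

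Table 1 also schedules DBS every 6 months for untreated patients in the standard and simplified models. The simplified cell reads "Physical examinationAST, plateletsHBsAg,DBSevery 6 months" (words run together in the extracted text). The corresponding test-and-treat cell is marked not applicable.

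The Statistical analysis section specifies a Cox model adjusted for baseline covariates, including age, sex and cirrhosis, for the primary outcome. It names no between-model test for suppression.

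**The concern.** The exposure under study, the model of care, determines which patients have an HBV DNA result. Conditioning on having been treated therefore selects a different slice of the CHB population in each model. This is selection produced by the treatment rules, and randomizing the sites would not have removed it.

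The reader of the results will see three suppression percentages in a paper about which model is best. A gap between them could arise with identical drug effect and identical adherence in comparable patients. A true difference in delivery could equally be masked. The limitations in the Discussion concede the non-randomized design but do not mention this mechanism.

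Adjustment can recover only part of the problem. Table 1 does not require AST, ALT or platelets in test-and-treat, so the APRI and ALT criteria that select patients elsewhere may not be available there for matching or standardization. No baseline HBV DNA measurement is described.

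**Working it through.** The protocol states no figure for viral suppression, so there is none to reproduce. The 997 per arm belongs to the primary outcome and plays no part here.

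**Step 1. Who has an HBV DNA result.** This follows from Table 1 and the Outcomes section.

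| Model | Assayed group |
|---|---|
| Standard | patients meeting a risk criterion |
| Simplified | all except the low-risk group |
| Test-and-treat | all treated patients, in principle everyone |

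One more mismatch comes from the section on pregnant women. Women in any model receive treatment late in pregnancy and may stop later if they meet no criterion of their own. In the standard and simplified models such women have received treatment but may be off it at 3 years. In test-and-treat every woman meets the model's criterion.

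**Step 2. Size of the artefact.** Let f be the share treated in the standard model, s the on-treatment suppression in those patients, and L the on-treatment suppression in everyone else. Assume s, L and the case mix are the same in every model.

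- Treated-only rate, standard: s
- Treated-only rate, test-and-treat: f·s + (1 − f)·L
- Difference: (1 − f)(L − s)

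The difference is zero when L = s, positive when L > s and negative when L < s.

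**Step 3. Illustration.** The values of f, s and L are assumptions, as is the figure of 1,000 evaluable patients per model. L = 0.95, and z is the difference divided by the square root of [s(1 − s)/(1000f) + t(1 − t)/1000], where t is the test-and-treat rate.

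| f | s | Test-and-treat rate t | Difference | z |
|---|---|---|---|---|
| 0.3 | 0.80 | 0.3×0.80 + 0.7×0.95 = 0.905 | 0.105 | 4.2 |
| 0.4 | 0.80 | 0.4×0.80 + 0.6×0.95 = 0.890 | 0.090 | 4.0 |
| 0.5 | 0.85 | 0.5×0.85 + 0.5×0.95 = 0.900 | 0.050 | 2.7 |

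These z values treat patients as independent. Care is assigned by site, with two sites per model, so they overstate the evidence.

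**Step 4. Sensitivity to the assumptions.** With L = 0.90, s from 0.60 to 0.80 and f from 0.2 to 0.6, the difference runs from (1 − 0.6)(0.90 − 0.80) = 0.04 to (1 − 0.2)(0.90 − 0.60) = 0.24. With 1,500 per model, a two-sided 5% test that ignores clustering rejects with probability 0.70 to 1.00. With s = L = 0.80 the difference is 0. If lower-risk patients were suppressed less often, say s = 0.95, L = 0.85 and f = 0.5, it would be 0.5 × (0.85 − 0.95) = −0.05.

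**Step 5. The denominator changes the quantity.** Assume 40%, 60% and 100% treated, s = 0.70 and L = 0.90.

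| Measure | Standard | Simplified | Test-and-treat |
|---|---|---|---|
| Treated only | 0.70 | (0.4×0.70 + 0.2×0.90)/0.6 = 0.767 | 0.4×0.70 + 0.6×0.90 = 0.82 |
| On treatment and suppressed, all enrolled | 0.4×0.70 = 0.28 | 0.28 + 0.2×0.90 = 0.46 | 0.82 |
| Suppressed, all enrolled, if 30% of untreated are at or below 10 IU/ml | 0.28 + 0.6×0.30 = 0.46 | 0.46 + 0.4×0.30 = 0.58 | 0.82 |

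The second row needs no assays beyond those planned. The third needs the untreated cards. Both depend heavily on the share treated, which the rules set.

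**The case against.** The strongest reply is that the protocol does not commit to the flawed comparison. Statistical analysis assigns the between-model analysis to the primary outcome, and the Outcomes section says which specimens are assayed without defining an analysis denominator. Denominators and adjustment for a secondary endpoint normally belong to the analysis plan, which the protocol says will be written. This stands as far as it goes: a treated-only test between models is an inference from the fourth objective read with the study's comparative aim. It does not remove the point, because the assay restriction is stated, and an analysis plan cannot adjust with HBV DNA that was never measured.

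A second reply is that treated-only suppression is a sensible measure of on-treatment response, while an all-enrolled rate largely restates the share treated. Both halves are fair. The treated-only rate should be kept as a within-model description, and an all-enrolled rate needs the share treated beside it.

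A reader might go further and infer that test-and-treat will look better because it adds patients who are easier to suppress. The documents do not support that. The criteria in Table 1 concern liver injury and risk, not viral load or adherence, and no suppression rates are given. Nor does it follow that the fourth objective is unanswerable: it also covers HIV incidence, which this assay restriction does not touch.

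**Conclusion.** The point holds as a selection problem built into a stated measurement rule. Any between-model reading of treated-only suppression compares groups that differ by construction, and the data required in test-and-treat limit adjustment. Non-comparability follows from the documents alone; size and direction do not. The 5 to 10 points rest on assumed suppression of 80–85% versus 95% and on 30–50% treated in the standard model. Other assumptions give anything from zero to larger gaps, or a gap of the opposite sign. Only the suppression part of one secondary objective is affected, so this should be corrected but does not threaten the main result.

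**What to change.** In the Outcomes section, state that suppression among treated patients is a within-model, descriptive measure of on-treatment response and will not be used to compare models. For any between-model comparison, define the endpoint over all enrolled participants, for example on treatment and suppressed at 3 years, and report it with the share treated in each model. The definition should say how it counts women treated only in pregnancy and participants whose treatment was stopped after repeated negative HBsAg tests. This costs wording only and uses the planned assays. It can still be made, since recruitment was ongoing when the article was written and the assays follow the 3-year observation period.

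Optionally, assay the 3-year DBS cards from untreated participants, all of them or a random sample weighted back, to estimate suppression in the whole cohort. The cost is assay cartridges, which sampling reduces. Two limits remain. Untreated people with naturally low HBV DNA would count as suppressed. Anyone who declines treatment in test-and-treat has no untreated DBS schedule in Table 1 and could go unmeasured.

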### Implementation research

The implementation objects will be the three different models of CHB care. We will begin by conducting a study of the context where the implementation will take place, and identify context-related barriers and facilitators [22]. Context is defined as a set of characteristics and circumstances that consist of active and unique factors, within which the implementation is embedded [16]. Setting on the other hand is the specific physical location, in which the intervention is put into practice and interacts with context and implementation [16]. For this purpose, we will use the Context and Implementation of Complex Interventions (CICI) [16] and Consolidated Framework for Implementation Research (CFIR) framework as a theoretical guide [23]. Identifying contextual barriers and facilitators of implementation will help to tailor appropriate strategies to mitigate the barriers and cultivate the facilitating factors [16]. We will then evaluate the process of implementation of complex intervention of the CHB treatment and care program. Implementation evaluation provides additional information on how different structures and resources are used, the roles of implementation agents, and the reasoning of various actors [14, 15, 24]. In general, process evaluation is how we can assess the success of implementation strategies, while outcome evaluation evaluates the success of the intervention [25]. In this process evaluation, we will answer the overarching question, ‘What factors influence their implementation process and success?’ We answer this question by assessing important indicators of implementation effectiveness, such as community screening, health education, and linkage to care.

Finally, we will assess implementation outcomes with appropriate implementation science methodologies. Implementation outcomes include acceptability, reach, feasibility, fidelity, adoptability, sustainability, and cost-effectiveness of the program [13, 26].

### Statistical analysis 

Results will be reported using descriptive statistics. Continous data will be reported as mean with standard deviation (SD), and categorical data as number with percentage. Cox proportional hazards regression models will be used to analyze the primary outcome (death and liver decompensation). The primary purpose of the analysis is to assess the association between the model of care and time to event, accounting for potential confounding factors. We will estimate hazard rations (HR), and 95% confidence intervals (CI) for the association between care model type (standard, simplified, test-and-treat) and the outcome. The model will be adjusted for baseline covariates known to be associated with adverse outcome, including age, sex and liver cirrhosis. The proportional hazards assumption will be tested using Schonefeld residuals. Individuals lost to follow-up will be right-censored at the last data known to be alive. Unadjusted survival functions will be estimated using Kaplan-Meier methods and compared using the log-rank test. A sensitivity analysis assuming that all individuals with missing outcome data at the end of the observation period reached the primary outcome (worst case scenario) will be performed.

In a secondary analysis, we will compare outcome variables in the decentralized models with previous results from a centralized model [4]. This comparison will have its inherent limitations due to differences in demography, co-morbidity, and available resources, which we can only partly adjust for in statistical models. However, it will still be of value to be able to assess the decentralized models in a wider context.

STATA (College Station, TX, USA) and/or R Core Team (2024) will be used to analyze the data.

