**Fig. 1 Fig1:**
[figure not shown]
Map of Ethiopia, with the 12 regional states. The study sites are illustrated with red dots. Original image from www.wikipedia.com, reproduced and adapted accordinly to the creative commons attribution-share alike 4.0 international license (https://commons.wikimedia.org/wiki/File: Regions_of_Ethiopia_EN.svg)

Two sites will be assigned to the standard model of care («treat only if…»), two sites to the simplified model of care («treat all except…»), and two sites to the test-and-treat model («treat all»). Each model will include one site situated in the Oromia region and one in the Somali region.

The final selection of the study sites were done in close collaboration with the regional health bureaus in the Oromia and Somali regions. As the study aimed to assess care in rural areas, primary hospitals or health centers in rural areas of these regions were considered. Only primary hospitals or health centers having an ART clinic were considered, leveraging the capacity for screening, counselling, initiation of antiviral treatment, long-term follow-up, and tracing efforts in cases of loss to follow-up. Furthermore, sites assigned to the standard or simplified model were required to have access to standard laboratory services such as hematology and biochemistry (ALT, AST) analysis.

Thus, participants will be recruited from the following six sites:

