### Sample size and duration of the study

The sample size has been calculated for the primary outcome (death or liver decompensation) with 80% power and 5% risk of type I error. We anticipate that 5% of all included patients (treated and untreated) will either die or experience liver decompensation within 3 years, with the standard model [20], and we want to detect a 50% relative reduction (Odds Ratio of 0.5 or less) with the test-and-treat model. This results in a sample size of 997 patients per arm [21]. We will increase the sample size by 50% and aim for 1,500 patients per model of care arm, due to expected attrition. This results in a total of 4,500 patients at six different sites. Assuming that approximately 9% of those living in the study setting are hepatitis B surface antigen (HBsAg) positive and 50% of those screened can be included in the study, we estimate that we need to screen approximately 100,000 individuals in order to enroll 4,500 CHB patients.

As inclusion rates may vary across sites, we plan to continue inclusion until all models of care have reached 1500 inclusions, accepting an uneven distribution between the two clinics assigned to the model. We expect to complete inclusion within 1 year. As the observation period will be three years, the total study period will be four years. The first participant was enrolled at September 5, 2024, and recruitment is ongoing. 

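### Care model is assigned to six sites, but the primary Cox model and the sample size treat patients as independent, so the hazard ratio intervals are too narrow unless sites do not differ in risk

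*Protocol article*

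**What the plan says.** **Assignment.** The Study setting section allocates whole sites to care models, two sites to each, and adds: "Each model will include one site situated in the Oromia region and one in the Somali region".

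**Enrolment.** Under Sample size and duration of the study, recruitment runs until each model has 1,500 patients, "accepting an uneven distribution between the two clinics assigned to the model".

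**Sample size.** The calculation is made "with 80% power and 5% risk of type I error". Its inputs are "We anticipate that 5% of all included patients (treated and untreated) will either die or experience liver decompensation within 3 years" under the standard model, and the aim to "detect a 50% relative reduction (Odds Ratio of 0.5 or less) with the test-and-treat model". The outcome of that calculation is given next: "This results in a sample size of 997 patients per arm". The later rise to 1,500 is attributed to attrition alone.

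**Analysis.** The Statistical analysis section gives the primary outcome to Cox regression: "The model will be adjusted for baseline covariates known to be associated with adverse outcome, including age, sex and liver cirrhosis". Beside it, "Unadjusted survival functions will be estimated using Kaplan-Meier methods and compared using the log-rank test". Site, region, frailty, cluster variance and stratification are not mentioned for either.

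**Acknowledged limits.** The Discussion concedes that, without cluster randomisation, baseline comparability of the models is not assured. It does not mention what two sites per model do to precision. A data analysis plan is still to be written (Oversight, monitoring and dissemination).

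**The concern.** The exposure varies only between sites, so the information on a model effect is limited by the number of sites, however many patients each enrols. Patients at one site share local screening venues, a facility type, a study team and a set of health extension workers who verify deaths. The sites are visibly unlike: one is a health centre with a single physician and the others are hospitals, and stated catchments run from about 50,000 to 1,500,000. A Cox model with independent patients puts none of the remaining between-site variation into its standard error.

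Region raises a second, conditional issue. The design gives every model one site per region, but the free split of enrolment means that the regional mix may differ between models, and region is not a named covariate.

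The Discussion says that a model found superior could be considered for use in other countries of the region. A falsely narrow interval would feed directly into that claim.

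**Working it through.** **1. Is a clustering allowance hidden in the plan's own figure?** Inputs from the sample size section: p1 = 0.05, p2 = 0.025, 5% type I error (two-sided assumed), 80% power.
- Individual-level comparison of two proportions: n = [1.96·√(2·0.0375·0.9625) + 0.842·√(0.05·0.95 + 0.025·0.975)]² / 0.025² = 906 per arm.
- With continuity correction: (n/4)·[1 + √(1 + 4/(n·0.025))]² = 984, which is 1.3% below the stated 997.
- 997 × 1.5 = 1,495.5, about 1,500, and the protocol gives that increase to attrition.

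So 997 is close to an individual-level figure with design effect 1, and no clustering allowance is hidden in it.

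**2. Effect on the error rate.** Inputs: 997 / 2 ≈ 499 evaluable patients per site and risk p = 0.05. The between-site CV of true risk is not in the documents; 0.1 to 0.3 is an assumption.
- Intracluster correlation: ICC = CV²·p/(1 − p)
- Design effect: DE = 1 + (499 − 1)·ICC
- True type I error of a nominal 5% test: 2·[1 − Φ(1.96/√DE)]

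| CV | ICC | DE | Interval should be wider by | Type I error, formula | Type I error, simulation |
|---|---|---|---|---|---|
| 0.1 | 0.00053 | 1.26 | ×1.12 | 8.1% | 8.1% |
| 0.2 | 0.0021 | 2.05 | ×1.43 | 17% | 17% |
| 0.3 | 0.0047 | 3.36 | ×1.83 | 28% | 28% |

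The simulation used gamma-distributed site effects, two sites per arm and 499 patients per site. At CV 0 it gave 5.1%.

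**3. If part of the variance is regional.** Every model has one site per region, so with equal regional mixes the regional share cancels from the contrast. If half the variance is regional, ICC halves. At CV 0.1, DE = 1 + 498·0.000263 = 1.13 and the type I error is 6.5%. At CV 0.3, DE = 1 + 498·0.00237 = 2.18 and it is 18%.

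**4. Effect on power.** With 997 per arm and no continuity correction, power at ICC 0 is 84%. Once between-site variance is allowed for, it is 75% at ICC 0.0005 and 35% at ICC 0.005. These use normal critical values and are optimistic. Six sites on region and model leave 6 − 1 − 1 − 2 = 2 residual df, where t = 4.30, and 4.30/1.96 = 2.2.

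**5. Region, with no true model effect.** Regional risks and mixes are assumptions.
- Equal mix in every model: risk ratio 1.00, whatever the regional risks.
- Risks 4% and 6%, mixes 60:40 and 40:60: (0.6·4 + 0.4·6)/(0.4·4 + 0.6·6) = 4.8/5.2 = 0.92.
- Risks 3% and 7%, mixes 70:30 and 30:70: (0.7·3 + 0.3·7)/(0.3·3 + 0.7·7) = 4.2/5.8 = 0.72.

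The last case is separate from step 2: risks of 3% and 7% alone imply a between-site CV of 2/5 = 0.40, above the range used there. The 4% and 6% case implies 1/5 = 0.20, within it.

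**The case against.** The best reply is that this is an article, its covariate list is open, and a data analysis plan will follow, so handling of site and region may simply not be reported yet. For region much of this stands: it is unnamed, not excluded. For site it does not, because the sample size already commits the study to independent patients, and the acknowledged limitation covers comparability but not precision.

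A reader might infer more than the documents support:
- **That region confounds the model contrast.** Every model has one site per region. If all models lean the same way, or regional risks are equal, there is no such bias. The enrolment rule may weaken the balance; it does not by itself undo it.
- **That the log-rank test is a second primary analysis.** It is presented as an unadjusted companion to the Cox model, and omitting region is consistent with that description.
- **That every site difference in case mix is read as a model effect.** Adjustment for age, sex and cirrhosis removes part of it.

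It is also fair to object that remedies are limited. Site fixed effects are aliased with model. A sandwich variance or a random effect from six sites is weakly estimated. A within-region contrast compares one site with one site. These points shape the fix but do not rescue the stated intervals.

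**Conclusion.** The point holds for the primary Cox analysis and the sample size. Any positive between-site variance makes the stated hazard ratio intervals too narrow, and the 80% power holds only if that variance is zero. Under an assumed CV of 0.1 to 0.3, with about 500 evaluable patients per site and 5% risk, the true type I error is about 8% to 28%. It falls to about 6.5% to 18% if half the variance is regional and the regional mix is balanced.

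Regional bias is a conditional risk. It needs both unequal mixes between models and unequal regional risks; the scenarios shown give a spurious risk ratio of 0.92 to 0.72. The documents give no CV, ICC or regional risk, so these figures show sensitivity and are not predictions.

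**What to change.** In the Statistical analysis section, and in the data analysis plan still to be prepared:

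1. Stratify the Cox baseline hazard by region, and add a region-stratified log-rank test beside the unadjusted one.
2. Base the confidence interval for the model effect on a small-sample site-level analysis: six site-level log event rates, adjusted for the baseline covariates, regressed on region and model (2 residual df). Add a sensitivity range for the between-site CV of 0.1 to 0.3. Do not rely on a six-cluster sandwich variance or an estimated random effect alone.
3. Show the six site results and the within-region contrasts as descriptive only.
4. State that model and site effects cannot be well separated with two sites per model, that patient-level Cox p-values do not by themselves support superiority, and that the stated 80% power assumes no between-site variance.

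**Cost.** No extra data collection: site and region are known for every participant. The real cost is precision. The critical value alone rises from 1.96 to 4.30, so intervals will be much wider and the conclusion about superiority more cautious.
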